### Specific Aim 1 – To evaluate the differences in functional performance and subjective outcomes between non-articulating ESR, articulating ESR, and active plantarflexion ESR feet.

Hypothesis 1.1 Subjects will demonstrate improvement and preference for articulating ESR and active plantar flexion ESR feet over the non-articulating ESR feet for community mobility, particularly for those that regularly negotiate inclines and declines.

Hypothesis 1.2 Active plantar-flexion ESR feet will result in better performance metrics for mobility based outcome measures.

Hypothesis 1.3 Subjects will have decreased low back and proximal joint pain scores as determined by the visual analog scale within the Prosthetic Evaluation Questionnaire (PEQ) when using the active plantarflexion ESR foot.

Hypothesis 1.4 There will be no significant differences in functional outcome measures within all tested non-articulating ESR feet regardless of specific foot assigned.

Hypothesis 1.5 There will be no significant differences in functional outcomes within all articulating ESR feet tested regardless of specific foot assigned.

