## **Outcome Measures**

The battery of functional outcome measures and surveys/guided interviews delivered after each acclimation period is delivered by a local researcher. Functional outcome measures include the 6-Min Walk, TUG, 4SST,

Amputee Mobility Predictor (AmpPRO), stair assessment index (SAI), and hill assessment index (HAI). Surveys/guided interview include Prosthetic Evaluation Questionnaire (PEQ), Short Form-12 (SF-12), and Orthotics and Prosthetics User Survey (OPUS).

- **6-Min Walk:** This test measures the distance an individual can walk in 6 minutes without help or encouragement. The 6-minute walk test is valid and reliable metric. It correlates with physical function and functional capacity (26, 27). This test has been proven to have good inter-rater and intra-rater reliability in transtibial amputees (26).
- **TUG:** The TUG measures the time taken by an individual to stand up from a standard arm chair, walk a distance of 10 feet, turn, walk back to the chair, and sit down. The TUG is both reliable and valid in a population with unilateral transtibial and transfemoral amputation (28). Additionally, the TUG has also been used as a measure to determine risk of falling (29, 30). This measure has also shown to correlate well with other measures of physical functioning (31).
- **4SST:** The 4SST is a higher order complex task assessing dynamic balance (32, 33).
- **AmpPRO:** The AmpPRO is a 21-item instrument designed to measure basic prosthetic mobility of individuals with lower extremity amputation (34).
- **HAI:** The HAI is a rated qualitative scale on how an individual with lower limb amputation negotiates up and down an incline (35).
- **SAI:** The SAI is a rated qualitative scale for stair negotiation (35).
- **PEQ:** The PEQ is self-report visual analog scale-style questionnaire for persons with lower limb amputations who use a prosthesis. It is used to evaluate the prosthesis and life with the prosthesis. It consists of 82 items with nine functional domain scales including ambulation, residual limb health, utility, appearance, sounds, frustration, perceived response, social burden and well-being. The PEQ also contains items beyond the subscales including satisfaction, pain, transfers, prosthetic care, self-efficacy, and importance (36).
  - **PEQ-Addendum:** This is an addendum to the PEQ, and it is a self-reporting measure to assess any stumbles and/or falls that occur during study protocol participation.

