## **SAI: Data and Statistical Analysis**

*Hypothesis 1.1 Subjects will prefer articulating ESR and active plantar flexion ESR ankle-foot units over the non-articulating ESR option for community mobility, particularly for those that regularly negotiate inclines and declines.* Preference will be demonstrated in the PEQ mobility questions. Across the study population, outcomes will be assessed with descriptive statistics (i.e. means and standard errors) and compared between

each intervention prosthesis. Inferential statistics for ordinal data (SAI, HAI) will be conducted with a repeated measures Friedman test ( $\alpha=.05$ ) and a Dunn post hoc test at a 95% confidence interval. To analyze the bivariate relationships between the factors of interest and the outcome measures (SAI, HAI), t-tests will be performed.

*Hypothesis 1.2 Active plantar-flexion ESR feet will result in better performance metrics for mobility based outcome measures.* For each functional outcome measures (6-min walk, TUG, AmpPRO, SAI and HAI) we will perform a repeated-measures analysis of variance (ANOVA) to compare the 3 testing conditions. When the ANOVA reveals significant differences ( $p < 0.05$ ), we will apply pairwise comparisons using related pairs t-tests to identify the source of differences ( $p < 0.05$ ). We will compute the difference between a given pair of sessions for the subject groups and determine the mean difference for subject groups.

*Hypothesis 1.3 Subjects will have decreased pain scores as determined by the visual analog scale (VAS) within the Prosthetic Evaluation Questionnaire when using the active plantarflexion ESR ankle-foot prosthesis*

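### Hypothesis 1.1 names PEQ mobility as its preference measure but attaches all its inferential tests to the stair and hill indices, so the preference part and the incline clause have no stated test

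*Protocol*

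**What the plan says.** Hypothesis 1.1 is worded in two ways. Under Specific Aim 1 it reads "Subjects will demonstrate improvement and preference for articulating ESR and active plantar flexion ESR feet over the non-articulating ESR feet", with the addition "particularly for those that regularly negotiate inclines and declines". In the Aim 1 analysis section (headed SAI: Data and Statistical Analysis) improvement has dropped out: "Subjects will prefer articulating ESR and active plantar flexion ESR ankle-foot units over the non-articulating ESR option for community mobility", followed by the same incline clause.

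That section then names the measure: "Preference will be demonstrated in the PEQ mobility questions". Three procedures follow:

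- Descriptive comparison: "outcomes will be assessed with descriptive statistics (i.e. means and standard errors) and compared between" the prostheses.
- "Inferential statistics for ordinal data (SAI, HAI) will be conducted with a repeated measures Friedman test" at alpha .05, with a Dunn post hoc test.
- "To analyze the bivariate relationships between the factors of interest and the outcome measures (SAI, HAI), t-tests will be performed". The factors of interest are not named.

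The Outcome Measures section describes what the two indices capture. For the hill index: "The HAI is a rated qualitative scale on how an individual with lower limb amputation negotiates up and down an incline". The SAI is the equivalent rating for stairs. The PEQ is listed there among the surveys, separately from the functional measures.

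**The concern.** The endpoint that carries the preference claim and the endpoints that carry the tests are different. A rating of how someone walks a ramp in a given foot does not show that they prefer that foot. The Protocol's own preliminary data make this concrete: the section on the powered-ankle study reports roughly 50% user rejection despite measured functional and biomechanical gains.

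The incline clause is a second gap. To say that a benefit holds especially for regular incline users is to say that the difference between feet depends on incline use. That is a foot-by-incline-use interaction, and no procedure in the plan is stated as a test of it.

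The study exists to produce prescription criteria. Whether incline users gain more from a particular foot category is a direct input to such criteria. An SAP that followed the Protocol faithfully would inherit the mismatch, so this is more than detail left for later.

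**Working it through.** **Step 1. Does any stated analysis test PEQ mobility?**

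| Place in the Protocol | Procedure | Outcome | Tests PEQ mobility? |
|---|---|---|---|
| H1.1 | Means, standard errors | Outcomes generally | Descriptive only |
| H1.1 | Friedman, Dunn | SAI, HAI | No |
| H1.1 | t-tests | SAI, HAI | No |
| H1.2 | Repeated-measures ANOVA, paired t-tests | 6-min walk, TUG, AmpPRO, SAI, HAI | No |
| H1.3 | Spearman, mixed models, stepwise regression | Pain scores, functional variables | No |
| H1.4, H1.5 and Aim 1 power | Multilevel ANOVA | Functional measures | No (PEQ is a survey) |
| Aim 3 | Logistic regression | Preference by activity time | No (different definition) |

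**Step 2. Does any stated analysis test modification by incline use?** No interaction or subgroup comparison is given for any Aim 1 outcome. The demographic items listed for the first visit are age, height, weight, injury etiology and time as a prosthesis user. Incline exposure is not among them. The daily activity log belongs to Part 5, after Parts 2-4 are complete.

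**Step 3. The plan's own power figure.** The Power Analysis section gives over 98% for 120 subjects, SD 5 and a 3-unit difference. Take three conditions, largest difference 3, third mean midway: the sum of squared deviations is 3²/2 = 4.5 and the noncentrality is 120 × 4.5 / 5² = 21.6. Power is 99.0%, both as a one-way ANOVA and as a repeated-measures ANOVA at correlation 0. The stated figure reproduces, but it is for functional measures. No effect size, SD or power is given for PEQ mobility or for an interaction.

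**Step 4. What a t-test of overall scores by incline use would do (illustration).** Nothing here comes from the Protocol except the 120 subjects and three scores each. Assumed: 60 incline users and 60 others, total SD 1, within-subject correlation ρ of 0.5 or 0.8, two-sided 5%.

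- SE of a group difference in subject means: √[(1+2ρ)/3 × 2/60] = 0.149 (ρ = 0.5), 0.170 (ρ = 0.8).
- SE of the interaction contrast (mean of the other two feet minus non-articulating): √[1.5(1−ρ) × 2/60] = 0.158, 0.100.
- SE that a t-test assumes if the three rows per subject are pooled: √(2/180) = 0.105.

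| Scenario | t-test, subject means | t-test, pooled rows | Interaction test |
|---|---|---|---|
| Incline users 0.3 SD better on every foot, no modification | 41-53% | 71-74% | 5-6% |
| No effect at all | – | 17-23% | – |
| 0.4 SD extra benefit on two feet, no offset | 34-42% | – | 71-98% |
| Same, hidden by a lower baseline | about 5% | – | 72-98% |

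These are simulation results with 6,000 runs per setting. The formulas agree: for subject means 0.3/0.149 = 2.01 and 0.3/0.170 = 1.77, giving 51% and 42%; for the interaction 0.4/0.158 = 2.53 and 0.4/0.100 = 4.0, giving 71% and 98%. The last row was chosen to cancel: 0.4 on two of three feet averages 0.4 × 2/3 = 0.27 SD, and a baseline deficit of that size brings the overall difference to zero.

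**The case against.** Four points can be made for the plan.

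1. *The hypothesis is partly tested.* A reader might infer that following the plan leaves Hypothesis 1.1 wholly untested. The document does not support that. Under Specific Aim 1 the hypothesis includes improvement, and a Friedman test on HAI and SAI across the three feet addresses it. This stands and confines the point to preference and the incline clause.

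2. *The t-test is under-described rather than shown to be wrong.* A reader might also infer that it will compare incline users with others on scores averaged or pooled over feet, and take the percentages above as the plan's error rates. The Protocol states neither the factor nor how the three scores are handled. Under Hypothesis 1.2 it plans differences between pairs of sessions for subject groups; a t-test of such differences by incline use would be an interaction test. This stands as regards the t-test's form. It does not supply a test of preference, because the outcome would still be SAI or HAI.

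3. *Aim 3 covers the question.* Hypothesis 3.1 concerns preference among people who commonly meet ramps and hills, and the prediction model regresses preference on several domains. This softens the consequence for the prescription criteria. But preference there is activity time over 30 days with all three limbs available, not PEQ mobility, so it does not replace the test.

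4. *Detail may sit in an SAP.* True of model specification. It does not cover a Protocol that names one endpoint and assigns its tests to others.

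**Conclusion.** The point holds in limited form. PEQ mobility, the named measure of preference, has only a descriptive comparison. The incline clause has no stated test on any endpoint. The SAI/HAI t-tests concern a different endpoint and, if run on overall scores by incline use, would not test modification. The improvement part is tested by the Friedman procedure.

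This conclusion rests on reading the text and needs no numerical assumption. Its size in this trial cannot be computed, since the Protocol gives no effect size or variance for PEQ mobility and no proportion of incline users. The percentages show only the kind of error that one implementation would produce. Group split, effect sizes, correlation and the form of the t-test are all assumed, and the masked case was built to cancel.

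The change should be made, though nothing here invalidates the trial's other Aim 1 comparisons.

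**What to change.** 1. Give Hypothesis 1.1 one wording in both places, stating whether improvement is part of it and which endpoint carries each part.
2. Analyse PEQ mobility with a linear mixed model: foot category, period, regular incline use and foot × incline use as fixed effects, subject as a random effect. Test preference by two planned contrasts, articulating and active plantarflexion each against non-articulating. Test the incline clause by the interaction.
3. Replace the SAI/HAI t-tests with an ordinal mixed model of the same structure.
4. Define regular incline use in advance and record it at enrolment, before any study foot is issued.
5. State that Hypothesis 3.1 uses activity time as its preference measure and is a separate question.

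The cost is one added enrolment question, revised Protocol and SAP wording, and somewhat more modelling. Power for the interaction will be limited and depends on how many subjects are regular incline users, so it should be reported as an estimate with a confidence interval. A non-significant interaction should not be read as evidence that incline use is irrelevant.

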The PEQ contains a VAS for pain within the evaluation. Spearman correlations, a statistical measure of the strength of a monotonic relationship between paired data will be calculated to correlate data between pain and functional outcome values across the 3 groups. Linear mixed-effects models will be used to identify statistically significant differences in pain scores and functional outcome variables. In the case of significance, pair-wise comparisons will be tested for significance using linear contrasts with Tukey's Honestly Significant Difference or applying Bonferroni's correction. Finally, stepwise multiple regression will be performed with VAS pain as the dependent variable. The independent variables will be comprised of functional parameters and condition (foot type). Significance will be set at  $p < 0.05$ . Variables will be eliminated if  $p$  is  $> 0.1$ .

*Hypothesis 1.4 There will be no significant differences in functional outcome measures within all tested non-articulating ESR feet regardless of specific foot assigned.*

*Hypothesis 1.5 There will be no significant differences in functional outcomes within all articulating ESR feet tested regardless of specific foot assigned.*

Functional measures will be analyzed by multilevel (site) repeated measures analysis of variance. Because order of prosthesis will be randomized, there should be no order effect. However, order will be included in the initial analysis to test this assumption. When the ANOVA reveals significant differences ( $p < 0.05$ ), we will apply pairwise comparisons using related pairs t-tests to identify the source of differences ( $p < 0.05$ ).

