#### Power Analysis:

| Site                                                | n   | n for subset |
|-----------------------------------------------------|------------|---------------------|
| VA New York Harbor Healthcare System (NYC)          | 30         | 15                  |
| Walter Reed National Military Medical Center (D.C.) | 30         | 15                  |
| VA Puget Sound Healthcare System (Seattle)          | 30         | 0                   |
| James J. Peters VA Medical Center (Tampa)           | 30         | 0                   |
| TOTAL                                        | 120 | 30           |

Figure 7. Total Subjects per site to be seen over the course of 3 year period

#### Specific Aim 1

Functional measures will be analyzed by multilevel (site) repeated measures analysis of variance. Because order of prosthesis will be randomized, there should be no order effect. However, order will be included in the initial analysis to test this assumption. Assuming an alpha error rate of 5% and within-group standard deviation of 5, 120 subjects will provide over 98% power to detect a 3 unit difference between at least two of the ESR groups for each of the functional measures.

### Specific Aim 2

Kinematic and kinetic measures will be analyzed by multilevel (site) repeated measures analysis of variance. Because order of prosthesis will be randomized, there should be no order effect. However, order will be included in the initial analysis to test this assumption. Assuming an alpha error rate of 5% and within-group standard deviation of 10, 30 subjects will provide 72% power to detect a 6-unit difference between at least two of the ESR groups for each of the measures.

### Specific Aim 3

This analysis will be performed using paired t-test to determine correlations between prosthesis chosen as per SAM data and which functional outcome measures are indicative of that choice. Additionally pair t-test will be performed between kinematic and kinetic data to again correlate with the prosthetic choice of the subject as demonstrated through the SAM data. Finally all SAM data will be evaluated against the activity journal to determine the roll of a specific activity goal and a specific prosthesis.

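### Hypothesis 1.2 is tested on five outcomes, each at an unadjusted 0.05, so one favourable measure could be reported as support for the powered foot

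*Protocol*

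**What the plan says.** Hypothesis 1.2, under Specific Aim 1 of the protocol, reads: "Active plantar-flexion ESR feet will result in better performance metrics for mobility based outcome measures". Its analysis is in the section headed SAI: Data and Statistical Analysis: "For each functional outcome measures (6-min walk, TUG, AmpPRO, SAI and HAI) we will perform a repeated-measures analysis of variance (ANOVA"). The conditions compared are the three feet. The follow-up rule is: "When the ANOVA reveals significant differences ( $p < 0.05$ ), we will apply pairwise comparisons using related pairs t-tests", these again at p < 0.05.

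The Power Analysis section, Specific Aim 1, uses a 5% alpha, a standard deviation of 5 and 120 subjects, and claims over 98% power "to detect a 3 unit difference between at least two of the ESR groups for each of the functional measures".

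Two other passages touch the same measures. Under Hypothesis 1.1, "Inferential statistics for ordinal data (SAI, HAI) will be conducted with a repeated measures Friedman test" at 0.05. Under Hypothesis 1.3, mixed models cover pain and the functional variables, and "pair-wise comparisons will be tested for significance using linear contrasts with Tukey's Honestly Significant Difference or applying Bonferroni's correction". That adjustment concerns pairs of feet within one outcome. It does not act across outcomes.

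**The concern.** Hypothesis 1.2 is a single claim in one direction, but it has five chances to succeed, each at the full 0.05, and on each the powered foot has two possible comparators. A significant ANOVA may also come only from articulating against non-articulating feet, which says nothing about the powered foot.

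Mixed results are likely. In the protocol's own preliminary data the 6-minute walk improved with the powered device while average TUG times did not change. Under the stated rule that pattern could be read as support or as failure, and the choice could be made after the results are known.

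At stake is whether a reported advantage of the powered foot has the error rate that a nominal 0.05 suggests.

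**Working it through.** **Inputs.** From the protocol: five outcomes, three feet per subject, ANOVA at 0.05, gated paired t-tests at 0.05, n = 120, SD 5, difference 3. Assumed, because the protocol does not give it: the correlation r between outcomes, taken as equal for all pairs and varied from 0 to 0.9. The simulations also treat all five outcomes as normal, although the protocol calls SAI and HAI ordinal.

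**1. The protocol's power figure.** For a repeated-measures ANOVA with uncorrelated feet, the noncentrality is λ = n Σ(μ − mean)² / SD², with 2 and 238 degrees of freedom.
- Means 0, 1.5, 3: λ = 120 × 4.5 / 25 = 21.6, power 99.0%.
- Means 0, 0, 3: λ = 120 × 6 / 25 = 28.8, power 99.9%.

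Both agree with the stated figure of over 98%. Positive correlation between feet raises them.

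**2. Within one outcome.** With three conditions, requiring a significant ANOVA first holds the chance of any false pairwise finding at about 5% when no feet differ. In simulation, the rate of any significant pair matched the rate of any significant ANOVA to within 0.0001. Under that null the inflation comes from the number of outcomes, not from the t-tests.

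**3. Across five outcomes, no foot differs.** If the outcomes are independent, the chance of at least one significant ANOVA is 1 − 0.95⁵ = 22.6%. Simulation gives the correlated cases. It also counts the narrower error that bears on Hypothesis 1.2: a significant ANOVA plus a significant t-test favouring the powered foot over at least one comparator.

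**4. Powered equals articulating, and both clearly beat non-articulating.** The ANOVA gate is then open on every outcome, and the one remaining null pair is tested at 0.05 each time. A false result favouring the powered foot has probability 0.025 per outcome. Over five independent outcomes that is 1 − 0.975⁵ = 11.9%.

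| Error, at least one of five outcomes | One outcome | r = 0 | r = 0.5 | r = 0.8 | r = 0.9 |
|---|---|---|---|---|---|
| Any false foot difference (step 3) | 5% | 23% | 19% | 13% | 10% |
| False powered-better against at least one comparator (step 3) | 2% | 10% | 8% | 6% | 4% |
| False powered-better-than-articulating (step 4) | 2.5% | 12% | 9% | 6% | 5% |

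**5. Effect of an adjustment.** At 0.05/5 = 0.01 per ANOVA, the first row becomes 1 − 0.99⁵ = 4.9% (r = 0) and 4.3% (r = 0.5). With the paired tests also at 0.01, the third row at r = 0 becomes 1 − 0.995⁵ = 2.5%. ANOVA power at 0.01, from the λ values in step 1, is 95.6% or 99.2%.

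**The case against.** The strongest reply is that the protocol never claims a family-wise error rate. It works per measure throughout, and its Power Analysis does the same, so nothing is contradicted. The first objective is to learn which functional tests support prescription, so looking at several measures is part of the design. A hierarchy or decision rule could also sit in a statistical analysis plan that is not at hand. This stands in part: the absence of a named primary outcome is not by itself a fault here. What remains is what the protocol does fix, an unadjusted 0.05 on each of five measures for one directional claim. A later plan would have to change that text.

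A reader might infer that the error rate for Hypothesis 1.2 is 19%, several times the nominal 5%. The documents do not support that. The 19% counts any difference between any two feet and rests on an assumed correlation of 0.5. For a false powered-better finding the figure is about 8%: roughly four times the single-outcome rate of about 2%, but only 1.6 times 5%.

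A reader might also infer that these p-values directly set the prescription criteria. The section on developing the prediction model says otherwise: it models patient preference by logistic regression with stepwise selection. The results for Hypothesis 1.2 inform the wider objectives but are not the stated prescribing rule.

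Lastly, several passages specify other models for the functional measures, including a multilevel model with site and order and, under Hypothesis 1.3, mixed models with adjusted contrasts. None of them adjusts across outcomes.

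**Conclusion.** The concern holds in a limited form. Five outcomes at an unadjusted 0.05 leave the claim of Hypothesis 1.2 without error control across measures. With no true foot difference, a false powered-better finding has a probability of about 8% (4% to 10% over the correlations tried). Where the powered and articulating feet are equal and both clearly beat the third, a false advantage over the articulating foot has a probability of about 9% (5% to 12%). The rate for any false foot difference is about 19% (10% to 23%). All these ranges depend on the assumed correlation and on treating the outcomes as normal. The data remain usable either way. What needs settling, before results are seen, is which result counts as support.

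**What to change.** In the Hypothesis 1.2 paragraph of the analysis section, apply Holm across the functional-measure ANOVAs, carry the adjusted level into the gated paired t-tests, and state that the hypothesis is supported only by an adjusted-significant contrast favouring the powered foot. For the paired tests, 0.05/5 = 0.01 throughout is the safe level. Holm's later steps rise to 0.05, and in the situation of step 4 using them for the t-tests would leave about 1 − 0.995 × 0.99375 × 0.99167 × 0.9875 × 0.975 = 5.6% at r = 0, instead of 2.5%.

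Alternatively, the sponsor names in advance one primary measure and a fixed order of powered-foot contrasts, each at two-sided 0.05, and labels the other measures secondary. Which measure and which order are the sponsor's choice.

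The cost is wording, with no new data. Isolated nominal findings on single measures would no longer support Hypothesis 1.2. Per-measure power falls slightly: Bonferroni at 0.01 keeps at least 95.6% at 3 units, SD 5 and n = 120. Those inputs are generic and are applied alike to distances, times and ordinal scores, so the figure does not establish the power for any particular measure. A named primary tested at 0.05 loses no power on that measure.
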